**STUDY POPULATION**

**5.1. Inclusion criteria:**

1. Age 2.00-17.99 years (prior to 18th birthday),
2. Diagnosis of asthma, defined as an asthma or probable asthma diagnosis/asthma- like phenotype made by a physician (this includes ED physician) in a patient who in the opinion of the treating ED physician requires therapy for acute asthma in the ED (GINA asthma guidelines, 2024).59
3. Moderate-severe asthma after initial therapy with 3 treatments of inhaled salbutamol and ipratropium, defined as an eligibility PRAM ≥5, indicating a strong association with hospitalization.25

**5.2. Exclusion criteria:**

1)

*2)*

Receipt of IVMg within 24 hours prior to ED arrival.

Need for airway support on arrival. *(Airway support on arrival meeting exclusion criteria will include immediate need for high flow nasal cannula therapy, non- invasive CPAP/bi-PAP ventilation or invasive ventilation with endotracheal intubation, as decided by the attending Emergency Department (ED) physician. Supplemental oxygen therapy will not represent an exclusion criterion.)*

Known renal, chronic pulmonary, neurologic, cardiac or systemic disease: *these may influence outcomes after Mg*.

Known hypersensitivity to Mg sulfate. Previous enrollment in this study.

Poor mastery of English and/or French language precluding informed consent understanding.

No phone/email; unavailable for follow-up

3)

4)

5)

6)

7)

**5.3. Strategies For Recruitment and Retention**

We expect 6 Canadian Hospitals to participate in this study. The anticipated study duration is approximately 38 months. We anticipate an 8-month pre-enrollment period, patient recruitment will occur for approximately 26 months, and an estimated 4-month post-enrollment period.

The target sample size is 192 participants. We anticipate an accrual rate of 7-8 participants a month in Emergency Departments (ED) across all sites.

Children presenting to the collaborating EDs who meet eligibility criteria will be approached for enrollment when the research nurses are on duty/on call (days and

Version Date: June 25, 2025 (v3.0)

Page **16** of **54**

[figure not shown]

**MAGICIAN** Clinical Trial Protocol

evenings). Participating sites have research assistants in the ED who will pre-screen potentially eligible patients and ensure the miss rate is kept to a minimum.

As per our previous MAGNUM trial with a similar design, we estimate that only 15% of screened patients will participate: 75% will be ineligible and 50% of the remaining will decline consent or not join for other reasons.3 We shall adopt the MAGNUM enrollment schedule, with coverage by on-call research nurses, to enroll 192 patients with full data across 6 sites in approximately 26 months. This is achievable given that MAGNUM used the same eligibility criteria and entry asthma severity and randomized 729 children with full data at 7 centers in 5 years (21 patients/year/site). Thus, we anticipate annual enrollment of 109 eligible consenting children with full data based on annual asthma ED presentations **(Appendix F)** and a conservative estimate of 30% weekly hours coverage, 25% eligibility, 50% of those eligible not participating for refusals/other reasons, 5% non-compliance with intervention (crossover) and 1% loss to follow up.

**6.**

**STUDY INTERVENTION**

**6.1. Study Intervention Description**

Previously healthy children 2.00-17.99 years of age with acute asthma will have PRAM routinely measured in triage, as per usual practice. Children presenting with a PRAM ≥ 5 will be considered potentially eligible and will receive oral dexamethasone, predniso(lo)ne or IV CS in triage/shortly thereafter. They will also receive three salbutamol and ipratropium inhalations61 via Metered Dose Inhaler/valved holding chamber approximately 20 minutes apart, with medication doses and ipratropium indications depending on local practice. If the PRAM is ≥ 5 after the first bronchodilator treatment and the child has no co-morbidities,62 a consent to approach for research will be obtained. At the conclusion of the 3 baseline inhalations, the research nurse will confirm eligibility, confirm the eligibility PRAM score, and obtain informed consent. A topical anesthetic may be used at the IV if that is the practice at a given site and IV line will be inserted. Participants may also receive an IV fluid bolus, as per site ED practice, prior to the experimental therapy, to improve hydration and prevent hypotension.

Thereafter, the trained and intervention-blinded study nurse will enter the patient eligibility data into the database, obtain the next study kit assigned to the appropriate age group (<6th birthday vs age 6 years and older) from the study fridge and enter the study kit number in the database. Master lists will be provided to all participating research pharmacies which will permit the preparation of the study kits according to the randomization schedule. Prior to the start of the experimental therapy, the study nurse will measure the patient’s Baseline PRAM, respiratory rate, heart rate, blood pressure and oxygen saturation.

**6.2. Study procedures (Dosing and Administration)**

The study nurse will administer the assigned experimental therapy (IV Mg sulfate

Version Date: June 25, 2025 (v3.0)

Page **17** of **54**

[figure not shown]

**MAGICIAN** Clinical Trial Protocol

or normal saline placebo) over a 30-minute period. The patients, study nurses, ED physicians and investigators will be blinded to treatment assignment; the pharmacy will be unblinded. [The SickKids research pharmacist will provide a manual with instructions on how each pharmacy will prepare blinded numbered kits with Mg or 0.9% saline placebo, according to routine IVMg sulfate infusion protocols (**Section**

**6.4.3 Logistics of Blinding and Kit Making)**. Each site will receive requirements for drug accountability and handling].

**Mg dose:** The chosen Mg sulfate dose of 75 mg/kg is at the upper end of the recommended dose range63,64 and is needed to minimize the probability that a subtherapeutic dose led to lack of observed treatment effect. Children weighing ≤30 kg require larger IVMg dose/kg than their heavier counterparts.47,48 Therefore, we shall administer IVMg 75 mg/kg (up to 2.5 g) to patients weighing ≤33 kg and 2.5 g to those >33 kg. This regime has a reassuring safety record: two pediatric studies of IVMg have employed doses of 75-100mg/kg without adverse effects.15,20 In three pediatric studies of 75 mg/kg IVMg bolus followed by 40 mg/kg/hour for 4 hours, no child developed hypotension.47,48 Two participating sites (Ste Justine’s, McMaster) routinely use 75 mg/kg IVMg.

**6.3. Study Procedures (after Administration of Study Intervention)**

Following the 30-minute experimental infusion, participants will continue to receive inhaled salbutamol, supplemental oxygen and other asthma medications as clinically warranted. *To prevent contamination, the use of open-label IVMg will be strongly discouraged* until after primary outcome determination at 120 minutes. In the highly exceptional event of respiratory failure after the intervention, immediate open-label IVMg will be permitted with locally used Mg doses (**Section 6.6 Emergency Unblinding Procedure)**, but unblinding will not be needed because a 2nd Mg infusion is safe for normotensive patients.47-49,51,60 Because children with unstable airway will be excluded and other routine asthma co-therapies will be given if needed, we do not anticipate open-label IVMg use prior to this time. IV in the placebo group is both clinically reasonable and ethically defensible: as the eligible children have refractory asthma, their ongoing respiratory distress will justify an IV to provide the often inadequate hydration and a potentially beneficial therapy to alleviate respiratory distress. Many of these children will need to be hospitalized which is often accompanied by IVMg therapy, other IV bronchodilators, and hydration. Topical anesthesia may be used if that is the practice at a given site.

Disposition will be determined by intervention-blinded ED physicians. While there is no known association between Mg serum levels and the duration of Mg bronchodilator effect, all study patients will be observed for 3 hours, to ensure safety. As per guidelines, discharged patients will be prescribed inhaled salbutamol, oral CS and inhaled CS, using locally employed regimes and doses. Further care will be sought if salbutamol is given more often than every 4 hours or if respiratory status interferes with the usual activity. There will also be a standardized electronic/telephone follow up to ascertain outcomes at 72 hours post ED discharge

Version Date: June 25, 2025 (v3.0)

Page **18** of **54**

[figure not shown]

**MAGICIAN** Clinical Trial Protocol

home.

**6.4. Preparation/Handling/Storage/Accountability**

**6.4.1.**

**Acquisition and Accountability**

Pharmacies at each of the participating sites will be using IV Magnesium Sulfate and Normal Saline that is routinely used through their hospital supply and available in the Canadian market to prepare the study kits to be used for blinded randomization.

**6.4.2.**

**Preparation of Treatment allocation and storage**

The Hospital for Sick Children research pharmacy department will produce Master Randomization tables through randomize.net, stratified by site and age group (< 6years old vs ≥6 years old),52 employing permuted randomization of varying block sizes in a 1:1 ratio of Mg sulfate to placebo. Upon receiving consent, the study nurse will enter the patient eligibility data into the database and will obtain the next assigned study kit.

Master lists will be provided to all participating research pharmacies which will permit the preparation of the study kits according to the randomization schedule. Because IV magnesium sulfate has to be refrigerated at 2-8˚C, the experimental kits containing either IV Mg or normal saline will be stored in the ED research fridge.

**6.4.3.**

**Logistics of Blinding and Kit Making**

Each site will prepare consecutively numbered randomization kits, numbered

according to the site’s Master Randomization table.

Each kit will contain:

Version Date: June 25, 2025 (v3.0)

Page **19** of **54**

**Arm**

**Investigational Drug or Placebo**

**(Blinded Vial in Kit)**

**Dose**

**Active**

Magnesium Sulfate Injection

500mg/mL vial (5.5mL)

75 mg/kg, max 2.5 grams (x ml = y mg)

**Placebo**

Normal Saline (0.9%) injection vial (5.5mL)

Weight-based volume to be identical to Mg solution

(x ml = y mg)

[figure not shown]

**MAGICIAN** Clinical Trial Protocol

•

Magnesium Sulfate Injection 500mg/mL OR 0.9% sodium chloride injection

•

**Active Kits** will contain Magnesium Sulfate injection

•

•

Injection to be administered by intravenous administration Unblinded site pharmacy will repackage small batches of Canadian commercial magnesium sulfate injection (5.5mL) into 10mL empty sterile vials in a laminar air flow hood according to a detailed worksheet procedure in the Pharmacy Manual of Operations.

•

**Placebo Kits** will contain 0.9% sodium chloride injection

•

Unblinded site pharmacy will prepare small batches of Normal Saline (0.9%) injection (5.5mL) into 10mL empty sterile vials in a Laminar Air Flow hood according to a detailed worksheet procedure in the Pharmacy Manual of Operations.

•

The repackaged Magnesium Sulfate and compounded placebo vials will be given a 3-month expiry date.

During Kit assembly by the site pharmacy, identical labels will be placed on the blinded vials to ensure the integrity of the blind.

Blinded Numbered Randomization Kits will be assembled by the unblinded site pharmacy and made available to the Emerg Study RNs for storage in the research fridge/pharmacy department for use once a subject is eligible to be randomized.

•

•

In this Investigator initiated study, the numbered kits will be assembled and labeled in the local Research Pharmacy according to detailed kit making Standard Operating Procedures provided by the Coordinating Pharmacy at SickKids. All kits/products will have appropriate Clinical Trial labeling according to Canadian regulations.

**6.5. Measures to Minimize Bias: Randomization and Blinding**

**Treatment allocation:** The leading site pharmacy will use the randomize.net tool to produce the study Master Randomization tables, stratified by site and age group (< 6years old, i.e. prior to 6th birthday vs ≥6 years old as pre-schoolers may respond differently to asthma therapies),52 employing permuted randomization of varying block sizes in a 1:1 ratio of Mg sulfate to placebo. The study nurse will transcribe the assigned study kit numbers into the secure Health Canada-validated REDCap database.

Master lists will be provided to all participating research pharmacies which will permit the preparation of the study kits according to the randomization schedule.

Version Date: June 25, 2025 (v3.0)

Page **20** of **54**

[figure not shown]

**MAGICIAN** Clinical Trial Protocol

The patients, outcome assessors (study nurses, ED physicians) and investigators will be blinded to treatment assignment; the pharmacy will be unblinded. The SickKids research pharmacist will provide a manual with instructions on how each pharmacy will prepare blinded numbered kits with Mg or 0.9% saline placebo, according to routine IVMg sulfate infusion protocols (**Section 6.4.3 Logistics of Blinding and Kit Making)**. Each site will receive requirements for drug accountability and handling. Unblinding is unlikely and did not occur in MAGNUM. The active Mg and saline placebo are identical in volume, color, odor, and appearance. Further, children with unstable airway will be excluded and only 6% experience a mean BP drop 5mmHg after IVMg with fewer requiring intervention.10

Administration of open-label IV-Mg would highly increase the probability of study contamination and will be strongly discouraged until after 120 minutes after the start of the experimental therapy. Children not responding to/worsening after the experimental therapy will be given back-to-back administration of inhaled salbutamol, other required medications and supplemental oxygen if necessary. In the highly exceptional event of impending respiratory failure after the intervention (children with unstable airway on arrival will be excluded), immediate open-label IVMg will be permitted with locally used Mg doses, but unblinding will not be needed because a 2nd Mg infusion is safe for normotensive patients.47-49,51,60 (**Section**

**6.6 Emergency Unblinding).**

**6.6. Emergency Unblinding Procedures**

Unblinding should only be requested when the clinical treatment of the patient will be different by knowing which arm of the study the patient was previously on. This may occur in a highly exceptional scenario of a suspected respiratory failure accompanied by clinically significant hypotension requiring treatment during the experimental therapy (presumed to have occurred during experimental Mg), and continuation of the experimental therapy would be undesirable. Hypotension will be defined as systolic blood pressure <70 mm Hg +(age in years x2) in children 2-10 years old and as <90 mm Hg in those

>10 years old. The study PI/local PI and the study nurses will remain blinded.

Hypotension occurring after the experimental therapy will be treated as needed but does not require unblinding.

The following Emergency Unblinding procedure will be followed:

1. Treating Physician or RN should contact the local QI of the study for consultation to unblind. In the event they cannot be reached immediately go to the next step.
2. Contact the SickKids hospital pharmacy by phone. The Research Pharmacy is available Mon – Fri from 08:00 to 16:00 EST at [contact] ext. 1 and ask to speak to a Research Pharmacist. At all other times or on statutory holidays call [contact] and ask to speak to a Pharmacist about an unblinding.
3. Provide the patient’s study randomization number, reason for unblinding, your site and your name to the SickKids pharmacist who will then provide the unblinded study arm.

Version Date: June 25, 2025 (v3.0)

Page **21** of **54**

[figure not shown]

**MAGICIAN** Clinical Trial Protocol

1. Note that all patients whose therapy is unblinded must stop receiving the experimental therapy The ED physician will prescribe additional treatment as clinically appropriate.
2. The requesting physician should initiate Email communication within 24 hours detailing the request for Emergency unblinding and why. The email must inform the local PI and SickKids Research Pharmacist and Study Principal Investigator ([[contact]](mailto:[contact]))
3. The DSMC and REB will be advised of emergency unblinding within 48 hours of Sponsor becoming aware of the incident.

**6.7. Concomitant Therapy**

We are collecting medications given prior to arrival in the ED. This is to compare groups at baseline. During the study intervention of 30 minutes no other medications will be given. Following the 30-minute experimental infusion, participants will continue to receive inhaled salbutamol, supplemental oxygen and other asthma medications as clinically warranted. These medications will be collected as outlined in section 1.3 (SoA) in the case report form.

**7.**

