**Endpoints:**

Primary endpoint: PRAM score at 120 minutes post start of experimental therapy.

Secondary endpoints: PRAM, oxygen saturation, heart rate and resp rate 30, 60, 120, 180 minutes and blood pressure 10, 20, 30, 60, 120, 180 minutes after start of experimental therapy and unscheduled medical re-visits/hospitalizations for asthma 72 hours after ED discharge home.

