**Experimental Group Treatment**

**IV Mg sulfate** (**wt ≤33 kg: 75 mg/kg; >33 kg: 2,500 mg)**

**Control Group Treatment IV Normal Saline**

**Study Nurse** measures PRAM, RR, HR, BP, O2 sat @ Baseline (pre experimental Rx), BP@ 10’,20’,30’after start of experimental Rx), and PRAM, RR, HR, BP, O2 sat @ 30’,60’, 120’, 180’

Further bronchodilator/other therapy as clinically indicated after experimental infusion finished.

Disposition decision by ED MD

Electronic/paper health chart review and telephone/email follow-up at 72 hrs (+7days)

Version Date: June 25, 2025 (v3.0)

Page **9** of **54**

[figure not shown]

**MAGICIAN** Clinical Trial Protocol

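### Section 6.7 bars all other medications during the 30-minute infusion with no exception, so rescue bronchodilator for a normotensive child with plain asthma worsening is not expressly permitted in that window

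*Protocol*

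**What the plan says.** Section 6.7 sets the rule for the infusion itself: "During the study intervention of 30 minutes no other medications will be given". It does not mention physician judgment or rescue. Its next sentence places salbutamol, oxygen and other asthma drugs in the period after the infusion.

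Other sections place the treatment of ongoing or worsening asthma at the same point:

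- The schema (1.2): "Further bronchodilator/other therapy as clinically indicated after experimental infusion finished".
- Section 6.3: "Following the 30-minute experimental infusion, participants will continue to receive inhaled salbutamol, supplemental oxygen and other asthma medications as clinically warranted".
- Section 6.5: "Children not responding to/worsening after the experimental therapy will be given back-to-back administration of inhaled salbutamol".
- Section 7.1 gives oxygen and further inhaled bronchodilator for deterioration that follows the experimental therapy.

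Open-label magnesium is likewise worded for the time after the intervention, in 6.3 ("In the highly exceptional event of respiratory failure after the intervention, immediate open-label IVMg will be permitted with locally used Mg doses") and in 6.5 ("In the highly exceptional event of impending respiratory failure after the intervention").

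Three sections carry a general, untimed assurance that asthma co-therapy will be available when required: 2.3, 6.3 and 11.3. In 2.3 and 11.3 that assurance supports the statement that children on placebo are not endangered.

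**The concern.** Every child enrolled still has a PRAM of at least 5 after three bronchodilator treatments (5.1), so further respiratory worsening is a foreseeable event. The exclusion for airway support applies on arrival (5.2). Section 9.2 allows about one hour for initial therapy and about one more for eligibility, consent, IV placement and pre-hydration, so the infusion starts roughly two hours into care. Stability on arrival is therefore limited reassurance about the infusion window.

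If staff follow 6.7 literally, a normotensive child who worsens mid-infusion waits for salbutamol until the infusion ends. If the physician treats at once, section 11.7 makes that a protocol deviation, since it counts any noncompliance. Section 11.7 only requires the event to be logged and assessed, and it neither forbids nor penalises treatment. But needed care should not depend on staff departing from a written rule.

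**Working it through.** This is a check of wording, and the plan gives no figure to reproduce. For each relevant provision, the question is whether it expressly permits rescue bronchodilator during minutes 0 to 30 for a normotensive child with asthma worsening not attributed to magnesium.

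| Section | Time covered | Trigger | Express permission in this case? |
|---|---|---|---|
| 6.7 | During infusion | None; all other medications barred | No, it prohibits |
| 1.2 schema, 6.3 (timed sentence) | After infusion | Clinical need | No |
| 6.5, 7.1 (deterioration) | After experimental therapy | Non-response or worsening | No |
| 6.3, 6.5 (open-label magnesium) | After intervention | Actual or impending respiratory failure | No; also a different drug |
| 7.1 (stopping) | During infusion | Hypotension needing therapy, apnea, or an event put down to magnesium | No; treatment follows stopping, and plain asthma worsening is not named |
| 7.2, 11.3 (stopping) | During infusion | Low blood pressure | No |
| 6.6 | Example set during infusion | General test: "Unblinding should only be requested when the clinical treatment of the patient will be different by knowing which arm"; the example is respiratory failure with hypotension | No; further treatment follows unblinding and stopping the study drug |
| 2.3, 6.3, 11.3 (general assurance) | Not stated | Need | Not express; the infusion window is not mentioned |

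**Could 7.1 be stretched to fit?** Section 10.3.3 lists respiratory depression among possible magnesium effects, so a blinded physician could attribute some respiratory decline to the study drug. The same section puts respiratory distress with events related to asthma or viral illness. Plain asthma worsening therefore does not clearly meet 7.1.

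**Does the assurance in 6.3 settle it?** That sentence concerns the period before the 120-minute outcome, which is counted from the start of therapy and so includes minutes 0 to 30. That supports reading co-therapy as available throughout. However, the paragraph opens with care after the infusion, and the section is headed accordingly. The sentence is untimed, while 6.7 is specific and absolute, so it does not clearly override 6.7.

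**Size of the window.** The longest wait for worsening that begins at minute t is 30 − t minutes:

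- t = 0: 30 − 0 = 30 minutes
- t = 10: 30 − 10 = 20 minutes
- t = 20: 30 − 20 = 10 minutes

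This restates the infusion length as a ceiling. It is not an estimate of harm.

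**The case against.** The best defence is that a 30-minute pause in co-medication is a reasonable way to limit co-intervention while the study drug runs, and that the severe end is largely handled. Section 7.1 covers apnea and any event put down to magnesium. Section 6.6 applies a general test, with hypotension only as an example, and then leaves further treatment to the physician. Children needing airway support on arrival are excluded. Physicians would in practice treat a child who needs it. All of this stands, and it makes the gap narrow. It does not supply the missing permission.

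A reader might infer more than the documents support:

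- **That the protocol contradicts itself or denies rescue.** The untimed assurances can be read together with 6.7 as general permission. The text is unclear and in tension, but not flatly contradictory.
- **That nobody watches the child's breathing before minute 30.** The scheduled measurements are "PRAM, oxygen saturation, heart rate and resp rate 30, 60, 120, 180 minutes and blood pressure 10, 20, 30, 60, 120, 180 minutes", so the vital signs scheduled at 10 and 20 minutes are blood pressure only. But nursing staff give the infusion (1.2, 6.2), and the schedule of activities has seven marks for adverse event review. Column positions are lost in the text. If all seven fall in the eight columns from time 0 to follow-up, at most one column is unmarked, so at least one of the 10- and 20-minute visits includes that review.
- **That the schema, 6.3, 6.5 and 7.1 also need amending.** Those sentences correctly describe care after the infusion. The open-label magnesium wording is a separate matter from rescue bronchodilator.
- **That the primary result or power suffers.** Nothing in the documents allows such an effect to be shown or sized.

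**Conclusion.** The point holds as a minor safety clarification. Section 6.7 prohibits all other medications during the infusion without exception. No passage expressly permits rescue bronchodilator in that window for a normotensive child with asthma worsening not attributed to magnesium. As written, 6.7 also suspends the salbutamol on which the placebo-safety argument in 2.3 and 11.3 relies.

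The exposure is at most 30 minutes per child. How many children it would affect is unknown, because the protocol gives no rate of worsening during the infusion and none is assumed here. The conclusion rests on reading 6.7 literally, as site staff working from the protocol might. It does not assume that any physician would in fact withhold treatment.

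**What to change.** Add one sentence to 6.7, directly after the prohibition:

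> Except that, if the treating physician judges that asthma is deteriorating during the infusion, rescue bronchodilator, oxygen or other needed therapy may be given at once; it is recorded as concomitant therapy, is not a protocol deviation, and the child remains in the ITT analysis.

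Retaining the child fits the intention-to-treat approach already adopted in 9.5. No change is needed in the schema, 6.3, 6.5 or 7.1.

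The cost is one sentence of amendment wording, with no extra patients, visits or procedures. The downside is a small amount of co-intervention inside the infusion window in children who need rescue, the extent of which cannot be estimated from the documents.
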